### 2.10. Sample Calculation

The sample size power calculation was based on data from previous studies that used tDCS associated with motor training in people with PD (Manenti et al., 2016). The power calculations used to determine the number of participants in each group were made in relation to the expected change in functional mobility (primary outcome). Thus, a calculation considering *p* < 0.05 and 90% power as significant suggests that at least 46 patients would be necessary. Considering the possibility of sample losses throughout the study, we will aim to recruit 56 patients, totaling 28 participants per group.

### 2.11. Data Analyses

The Statistical Package for the Social Sciences (SPSS), version 27.0, will be used in data analysis and a 5% alpha (*P* < 0.05) will be established.

The groups will be compared using the Student's *t*-test or Mann-Whitney test, for continuous variables, or the chi-squared test for categorical variables, according to the normality distribution, analyzed using the Shapiro-Wilk test. The primary outcome will be examined with a repeated measures split-plot ANOVA, with one dependent and two independent variables: one intragroup (time, with 3 levels: T0, T1 and T2), and one intergroup (a group with two levels: CG and EG) using Sidak's *post hoc* test. Analyses of covariance (ANCOVA) will be used to identify significant intergroup differences applying T0 scores as covariables. Linear regression will be used to identify response predictors. The independent variables will be group and clinical response, that is, the minimal clinically important difference (MCID). An intention to treat analysis will be conducted.

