**Figure 1 F1:**
[figure not shown]
Schedule of enrollment, interventions and assessments demonstrated in the Standard Protocol Items: Recommendations for Interventional Trials (SPIRIT).

The treatment program for patients with PD will involve 12 sessions, three times a week. Study participants will be assessed at three different times: 4–7 days before the first intervention session, which will consider the baseline reference measure (T0); 4–7 days after the last session, considered a post-intervention measure (T1); and 30 days after the last intervention session, considered a post-intervention or follow-up measure (T2). Figure 2 illustrates the study design.

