### 2.7. Outcomes

The primary outcome will be functional mobility, measured using the Timed Up and Go test (Podsiadlo and Richardson, 1991), to stand up from a chair at the command: “Walk 3 meters, walk along a demarcated course, turn around and walk back to the chair, then sit down”. For secondary outcomes, the following instruments will be used to assess executive function: (1) Wisconsin Card Sorting Test (WCST) to assess planning, cognitive flexibility, working memory, monitorization, inhibition of perseverations, and aspects related to executive function (Heaton and Staff, 1993); (2) Stroop Test, to assess selective attention, inhibition, cognitive flexibility, processing speed, fluid intelligence and the semantic system (Lezak et al., 2004, Strauss et al., 2006); (3) Trail Making Test (TMT), to evaluate the ability to draw lines between consecutive numbers from 1 to 25 (Bowie and Harvey, 2006); (4) Verbal Fluency Test to assess semantic and phonemic fluency in 1 min (Brucki and Rocha, 2004); and (5) Montreal Cognitive Assessment(MoCA), to evaluate overall cognitive and executive function (Van Uem et al., 2016).

The following scales will be used to assess motor function: (1) Dynamic Gait Index (DGI), to assess eight aspects of gait as well as dynamic balance (Shumway-Cook et al., 2000); (2) 10-meter walk test, to estimate gait speed by recording the average time the patient takes to cover a distance of 10m in three attempts (Peters et al., 2013); (3) Borg Scale, to guide physical activity intensity level and measure perceived exertion during session training (Borg, 1982); (4) Sit-to-stand (STS) test; (5) Kinematics of Gait, to analyze movement using the Qualisys Motion Capture System (Qualisys Medical AB, 411 13, Gothenburg, Sweden). This system records the spatio-temporal variables of gait, as well as the angular variations of the hip, knee and ankle joints; (6) MiniBESTest, to measure aspects of static and dynamic balance (Franchignoni et al., 2010); (7) Revised Movement Disorder Society-Sponsored Revision of the Unified Parkinson's Disease Rating Scale (MDS-UPDRS), to assess motor function (Goetz et al., 2008); and (8) Short FES-I, to measure the level of confidence in performing daily activities, in addition to identifying fear of falling and possible social isolation (Kempen et al., 2008). All the instruments used to assess the primary and secondary outcomes are described in Table 1.

**Table 1 T1:** Primary and secondary outcome measures.

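### The primary TUG analysis treats baseline as an outcome level and fixes neither the deciding contrast nor the deciding visit

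*Protocol article*

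**What the plan says.** All references are to the protocol article.

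- **Outcome (2.7).** "The primary outcome will be functional mobility, measured using the Timed Up and Go test". Table 1 lists TUG at all three assessments and marks none as primary.
- **Visits (2.1).** T0 precedes the first session, T1 is "4–7 days after the last session, considered a post-intervention measure (T1"), and T2 is 30 days after the last session.
- **Primary method (2.11).** "The primary outcome will be examined with a repeated measures split-plot ANOVA, with one dependent and two independent variables": time (T0, T1, T2) within patients and group (CG, EG) between patients, with Sidak post hoc tests.
- **Second between-group test (2.11).** "Analyses of covariance (ANCOVA) will be used to identify significant intergroup differences applying T0 scores as covariables". The sentence names neither an outcome nor a visit, and does not say how this test ranks against the ANOVA.
- **Significance level (2.11).** "a 5% alpha (*P* < 0.05) will be established". Sidak is mentioned only for the ANOVA post hoc tests.
- **Sample size (2.10).** The calculation was "made in relation to the expected change in functional mobility (primary outcome"), and "a calculation considering *p* < 0.05 and 90% power as significant suggests that at least 46 patients would be necessary". No effect size, SD, correlation, test or visit is given. For losses, "we will aim to recruit 56 patients, totaling 28 participants per group".

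**The concern.** A split-plot ANOVA with these factors gives a group main effect, a time effect, a 2-df interaction and a set of post hoc contrasts. Only some of these address whether dual-task training changes TUG, and the article does not say which one answers the trial's question.

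Two different harms follow, depending on how the gap is filled.

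- **If the ANOVA decides, power is at risk.** T0 is measured before treatment, so its true between-group difference is zero under randomisation. Averaging it into the group main effect dilutes the effect. The interaction avoids that dilution but spreads the question over two degrees of freedom.
- **If nothing is designated, the false-positive rate is at risk.** A positive claim could rest on whichever of several tests or visits reached P < 0.05.

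These harms are alternatives and do not add up. Either one leaves the primary hypothesis undefined. A report of a positive result at T1 by ANCOVA, and one at T2 by a Sidak contrast, would both be consistent with the text.

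**Working it through.** **Inputs from the article.** Alpha 0.05 (two-sided assumed); 46 patients needed, so 23 per arm; three visits; two arms, 1:1.

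**Assumptions, because the article gives no figures.** Unit SD at each visit, normal data, equal correlation r between visits of 0.5 to 0.8 (some checks go to 0.85 or use unequal correlations). The effect at T1 is d = 0.5 SD, either fully sustained or half retained at T2. Each setting used 20,000 simulated trials.

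**The stated sample size.** The 46 cannot be reproduced without an effect size. Back-solving a plain two-group comparison at 90% power gives d = √[2(1.960 + 1.282)²/23] = √(21.02/23) = 0.956. This is an illustration and not the article's own input.

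**Dilution of the group main effect.** The main effect compares the three-visit means.

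- Sustained: (0 + d + d)/3 = 2d/3.
- Half retained: (0 + d + d/2)/3 = d/2.

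Normal approximation at r = 0.7, d = 0.5, sustained:

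- Main effect: SD of the three-visit mean = √[(1 + 2r)/3] = √0.8 = 0.894. Signal = (0.333/0.894) × √(23/2) = 1.26. Power ≈ Φ(1.26 − 1.96) = 24%. Simulated: 23%, and 15% if half retained.
- ANCOVA at T1: residual SD = √(1 − r²) = √0.51 = 0.714. Signal = (0.5/0.714) × √(23/2) = 2.37. Power ≈ Φ(2.37 − 1.96) = 66%. Simulated: 63%.

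**Interaction against ANCOVA at T1 (d = 0.5, 23 per arm).** Simulated values, good to about one percentage point. ANCOVA at T1 does not depend on what happens at T2.

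| r | Interaction, half retained | Interaction, sustained | ANCOVA at T1 |
|---|---|---|---|
| 0.5 | 30% | 38% | 47% |
| 0.7 | 47% | 60% | 63% |
| 0.8 | 65% | 78% | 78% |

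The ordering can reverse. At d = 0.6 sustained and r = 0.85 the interaction has 97% against 96%. With d = 0.5 at T1 only and correlations T0–T1 0.7, T0–T2 0.7, T1–T2 0.85, it has 68% against 63%. At d = 0.956 sustained and r = 0.7 both have 99%.

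**Type I error under the null.** Each test alone rejects in about 5% of trials. If any significant result in a set counted:

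| Set of tests | Simulated | If independent |
|---|---|---|
| Interaction, ANCOVA at T1 | 7.3–8.3% | 1 − 0.95² = 9.8% |
| ANCOVA at T1, ANCOVA at T2 | 9.0–9.6% | 9.8% |
| Interaction, both ANCOVAs | 10.1–11.0% | 1 − 0.95³ = 14.3% |
| The same plus group main effect | 14.2–14.7% | 1 − 0.95⁴ = 18.5% |

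The third row is for equal correlations of 0.5 to 0.8. Over all structures tried it runs from 9.3% to 11.2%.

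**One named contrast.** A single ANCOVA, at one visit or on the T1/T2 mean, had a simulated type I error of 4.6–5.3%. At d = 0.6 and r = 0.7, the mean has more power than T1 if the effect is sustained (90% v 78%) and less if half is retained (70% v 79%).

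**The case against.** A reader might infer that the plan, as written, inflates type I error and makes the weaker test primary. The documents do not support that.

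- **Inflation is conditional.** No rule says any significant result counts, although none excludes it. On a stepwise reading, with the interaction first and ANCOVA only to locate the difference, the error cannot exceed 5%; simulation of that rule gives 3.2–4.0%. Having T0 as a level does not in itself raise the error.
- **ANCOVA at two visits is inferred.** Its sentence names neither TUG nor a visit. TUG is the natural reading, because the sentence follows directly on the primary analysis. The 10–11% figure depends on the further step of testing both T1 and T2.
- **The two complaints exclude each other.** If the ANOVA is primary, ANCOVA adds no primary type I error. If nothing is primary, no weak test has been made primary.
- **The power deficit is not general.** The group main effect is the least favourable reading, since the interaction is the usual test of differential change. An effect of 0.5 SD is assumed, and at the back-solved 0.956, sustained, the gap is small or absent (92% v 95% at r = 0.5; 99% v 99% at r = 0.7).
- **The article is condensed and calls the study exploratory.** Test ordering may be set out in a plan not shown.

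All but the last of these limit the size of the point and are accepted. The last carries less weight. The article does fix a primary method, and that method puts a pre-treatment value among the outcomes and leaves the primary contrast and visit open. These define the hypothesis, and an exploratory label does not settle them.

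**Conclusion.** The point holds in limited form. The article puts T0 among the outcome levels, does not name the deciding ANOVA term, adds an unranked ANCOVA and fixes no primary visit.

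- **Firm:** the group main effect is diluted to two thirds of a sustained effect. This follows from randomisation and needs no assumed correlation. Its power is low beside ANCOVA at T1 (28–37% v 62–96% at d = 0.6 sustained, r 0.5 to 0.85).
- **Dependent on assumptions:** the interaction is usually, not always, weaker than ANCOVA. The gap is widest when the effect fades by T2 and nearly closes when it is sustained and r is 0.7 or more.
- **Conditional:** a type I error of 10–11%, or 14–15%, arises only if any significant test may be claimed and ANCOVA is run at both visits.

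The effect on the stated 90% power cannot be calculated from the article's own inputs. The correction should be made. The individual tests are valid; the defect is that the primary claim is not tied to one of them.

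**What to change.** Before unblinding, name one deciding contrast: the EG–CG difference in TUG, adjusted for T0 TUG and for the freezing-of-gait stratum (section 2.4 stratifies the randomisation on it). Estimate it by ANCOVA, or by a mixed model with only T1 and T2 as outcomes.

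The sponsor chooses one target: a single visit (for example T1) or the T1/T2 mean. The mean suits an expected lasting effect and a single visit suits one expected to fade. If a single visit is chosen, the other visit is secondary.

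Label the split-plot ANOVA supportive, and do not use its group main effect as evidence of a treatment effect. State in section 2.10 which contrast and visit the 46 patients were meant to power.

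The cost is wording only: ANCOVA is already planned, and no patients, visits or data are added. The downside is that an effect seen only at the non-primary visit becomes a secondary result.

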tDCS is used to modulate cortical excitability, due to its action on neural membrane potential, leading to neuronal hyperpolarization via cathodic stimulation or depolarization provided by anodic stimulation (Nitsche and Paulus, 2000). Several studies show that in the rehabilitation of people with PD, tDCS has positive effects on motor function (Fregni et al., 2006), gait and bradykinesia (Benninger et al., 2010). When combined with physical training, tDCS can improve speed and balance during locomotion (Kaski et al., 2014) and seems to prolong the effects of motor intervention (Costa-Ribeiro et al., 2017).

Despite the promising results in reducing the symptoms of PD, the predictive factors that lead to a better response to intervention remain largely unknown. Disease severity, the medication dose in use, clinical type and freezing of gait seem to influence the effect and response to therapy. In relation to individual vulnerability, it is still unclear for whom these benefits apply, that is, whether age, disease severity or even emotional aspects linked to depression and anxiety before treatment determine treatment responsiveness (Carrarini et al., 2019). Moreover, the heterogeneity of the protocols used in the studies reflect the lack of understanding task-dependency associated with tDCS (Schoellmann et al., 2019). Which motor and cognitive components should be emphasized during tDCS-linked training has been little studied and whether multimodal protocols with mixed training should be prioritized over strictly motor or cognitive tasks.

In this clinical trial, we sought to investigate two aspects. First, to examine task-dependency in enhancing the effects of tDCS-linked rehabilitation training on PD. The relationships between baseline outcomes in responders and non-responders to therapy will also be examined, once, we also hypothesize that differences in clinical variables such as disease severity and depression symptoms may affect treatment effectiveness. In light of the evidence in previous studies (Swank et al., 2016; Manor et al., 2018), we hypothesize that a dual-task intervention program, including motor and cognitive paradigms, will be more robust in clinical measures than gait motor training alone.

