### 2.6. Screening

Study participants will be submitted to screening and an initial visit before being assessed for primary and secondary outcomes. A structured evaluation will be carried out, including sociodemographic data; time since diagnosis; disease severity according to the modified Hoehn and Yahr Clinical Staging Scale (Hoehn and Yahr, 1998; Goetz et al., 2004); medication doses used; levodopa equivalent daily dose (LEDD); symptoms of depression and anxiety, measured by the Hospital Anxiety Depression (HAD) scale; freezing of gait, assessed by the Freezing of Gait Questionnaire (FOG-Q) (Giladi et al., 2009); and type of disease, classified as akinetic-rigid, tremulant or mixed. Although of tremor-dominant and nontremor-dominant subtypes are the most comonly system used to defining Parkinson's disease subtypes, the participant's classification as postural instability gait disorder (PIGD) phenotype (or akinetic-rigid) has been used to specify a nontremor-dominant subtype (Marras, 2015). In this study, the participant's classification for PIGD score will be described based on “walking and balance” and “freezing” items of part II of Movement Disorder Society Unified Parkinson's Disease Rating Scale scores (MDS-UPDRS), and the “gait”, “freezing of gait” and “postural stability” items of part III of MDS-UPDRS scores (Jankovic et al., 1990). TD/PIGD scores will be used for all patients and calculate by dividing mean tremor subscores (2.10, 3.15a, 3.15b, 3.16a, 3.16b, 3.17a, 3.17b, 3.17c, 3.17d, 3.17 and 3.18) by mean PIGD subscores (2.12, 2.13, 3.10, 3.11 and 3.12) (Stebbins et al., 2013). Values equal to 1.15 classifiles the patient as TD subtype, whereas values equal to 0.90 represent PIGD. The patient will be classified as indeterminate subtype if the ratio between mean TD and mean PIGD valeus will be between 0.90 and 1.15 (Stebbins et al., 2013). The Mini-Mental State Examination (MEEM) will be applied in order to characterize the sample (Folstein et al., 1975). We will investigate lateral dominance aspects using the Edinburgh Handedness Inventory (Oldfield, 1971), and collect anthropometric data such as head circumference, inter-tragus and nasion-inion distance, height, weight and body mass index (BMI).

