## 3. Discussion

Progressive cognitive compromise in PD is considered a significant predictor of disability (Yogev-Seligmann et al., 2008) and an important cause for the decline in motor function (Lemes et al., 2016). This study aims at assessing the effectiveness of dual-task training and gait training conducted concomitantly with the neuromodulation protocol In addition, we intend to analyze the clinical factors and variability between individuals that could interfere in the training of a specific task and influence the therapeutic effect, acting as response predictors of the motor and cognitive function of people with PD.

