## Limitations and Advantages

Additional limitations should be noted. The estimated sample size may be limited. Nevertheless, our exploratory study is a step in the direction of large-scale studies. Furthermore, the study design enables secondary between-group analyses regarding baseline variables and predictors of treatment response. Finally, the study will provide robust results regarding the isolated and combined effects of tDCS and motor training.

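### The response-predictor regression lists clinical response as an independent variable and names no dependent variable, so it does not match the aim of finding baseline predictors of response

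*Protocol article*

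**What the plan says.** Section 2.11 of the protocol article gives the method and its purpose: "Linear regression will be used to identify response predictors". The next sentence gives the regressors: "The independent variables will be group and clinical response, that is, the minimal clinically important difference (MCID"). No dependent variable is stated, and no baseline characteristic appears among the regressors. Baseline values enter that section only through a different analysis: "Analyses of covariance (ANCOVA) will be used to identify significant intergroup differences applying T0 scores as covariables".

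The aim is described in three other places:

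- **Introduction:** "The relationships between baseline outcomes in responders and non-responders to therapy will also be examined", with the hypothesis that "differences in clinical variables such as disease severity and depression symptoms may affect treatment effectiveness".
- **Discussion, opening paragraph:** clinical factors and variability between individuals are described as "acting as response predictors of the motor and cognitive function of people with PD".
- **Limitations and Advantages:** "the study design enables secondary between-group analyses regarding baseline variables and predictors of treatment response". No model is given there.

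Section 2.6 collects the relevant variables at screening: modified Hoehn and Yahr stage, HAD depression and anxiety, levodopa equivalent dose, freezing of gait and motor subtype.

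**The concern.** Response is what the second aim sets out to explain. Section 2.11 places it among the explanatory variables and leaves out the baseline factors that are meant to explain it. Response is also known only after treatment and is derived from an outcome, so putting it on the right-hand side conditions on a post-randomisation quantity.

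At stake is the second of the two aims in the Introduction. An analyst following the sentence literally could report a strong predictor that is only the outcome restated. An analyst who departs from it must choose the dependent variable, the model type and the predictors without guidance from the text.

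**Working it through.** The plan states no figure that depends on this sentence, so there is none to reproduce. The check takes each possible dependent variable in turn. The simulations use assumed values, not trial data: 28 per arm, change = b × baseline + 0.3 × group + N(0,1), responder if change exceeds 0.5, and 3,000 runs.

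**Reading A: the dependent variable is a TUG-type change.** The model is change on group and responder status.

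| Model | Term tested | b = 0 | b = 0.5 |
|---|---|---|---|
| Change on group + responder status | responder status | significant in 100% of runs | significant in 100% of runs |
| Change on group + baseline factor | baseline factor | 5.3% | 93.7% |

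In the first model R² is about 0.62 to 0.63 whether or not the baseline factor matters. The fit is circular and carries no information on that factor. The group coefficient also shrinks: a true effect of 0.3 SD becomes about 0.11 to 0.12, and 0.9 SD becomes about 0.33.

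**Reading B: "independent" is a slip for dependent.** Responder status is binary, which does not suit the linear regression named. Group, the randomised factor, would become a dependent variable too. The predictors would still not be stated.

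**Reading C: the dependent variable is a baseline measure.** The model is baseline on group and responder status. The test of responder status is then a test of the partial correlation between baseline and response given group, and that correlation is symmetric. Its p-value is identical to that for the baseline factor when response is regressed linearly on group and baseline. In simulation both directions reject in about 5% of runs at b = 0 and in 76% to 77% at b = 0.5. This reading does test an association. It pools the arms, however, and has no group-by-factor term, so it cannot separate a factor that predicts outcome in everyone from one that changes the effect of dual-task training.

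**Power of the interaction that would address effect modification.** Inputs: N = 46 (section 2.10, evaluable patients) and two-sided alpha 0.05 (section 2.11 gives 5%; two-sided is assumed). Also assumed are a binary moderator with share p and a T0–T1 correlation r.

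- SE of the interaction, in SD units = √(1 − r²) × √(4 / (N p(1 − p))).
- With p = 0.5 and r = 0.6: 0.8 × √(16/46) = 0.8 × 0.590 = 0.472.
- 0.5 SD interaction: 0.5/0.472 = 1.06, noncentral-t power about 18%.
- 1.0 SD interaction: 1.0/0.472 = 2.12, power about 54%.
- Range for 0.5 SD, p = 0.5: r = 0.4 gives SE 0.917 × 0.590 = 0.541 and power about 15%; r = 0.8 gives SE 0.6 × 0.590 = 0.354 and power about 28%.
- A 30/70 split with r = 0.6: SE 0.8 × √(4/(46 × 0.21)) = 0.515, power about 16%.
- All 56 patients, p = 0.5, r = 0.6: SE 0.8 × √(16/56) = 0.428, power about 21% (0.5 SD) and 63% (1.0 SD).

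These figures describe the limits of a corrected analysis. They do not measure the defect itself.

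**Subtype wording, section 2.6.** "Values equal to 1.15 classifiles the patient as TD subtype, whereas values equal to 0.90 represent PIGD", and ratios between the two values are indeterminate. Read literally, a ratio of 1.5 or 0.5 has no class.

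**The case against.** The strongest reply is that the damage depends on a dependent variable that section 2.11 does not name. Under reading C the regression compares baseline values between responders and non-responders, adjusted for group, which is close to how the Introduction words the aim. That stands. A reader might infer that the aim is lost altogether, or that no baseline factor could be tested under any reading; the text does not support either conclusion.

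A slip of one word is also plausible, since the intended direction is clear elsewhere, and a condensed article may leave the full predictor list and the interaction terms to an analysis plan. That stands in part. The absence of a detailed list would not be a finding by itself. But the article does not leave the model open: it names the method and the regressors, and those disagree with its aim. The slip reading also leaves a binary outcome in a linear model.

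It can be added that the treatment effect is not taken from this regression. The primary TUG analysis is a split-plot ANOVA, with ANCOVA on T0 scores for intergroup differences. This is right, so the shrunken group coefficient under reading A should not be taken as bias in the main result. The Limitations section already calls the study exploratory and these analyses secondary.

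Finally, the hypothesis names only severity and depression, as examples. Medication dose, clinical type and freezing appear in the Introduction as background, and nothing makes subtype a planned regressor. The subtype wording is therefore a separate, nearly clerical matter and adds no weight here.

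**Conclusion.** The point holds as a should-fix on a secondary, exploratory analysis. The regression in section 2.11 contradicts the stated direction of the aim and names no dependent variable. It is circular under reading A, mismatched to its outcome under reading B, and at best an indirect test of association under reading C. In none of them does it model whether baseline factors modify the treatment effect. This conclusion comes from comparing sections of the article and needs no numerical assumption.

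The simulations only illustrate the mechanism. The 18% power rests on 46 evaluable patients, an even moderator split and a baseline correlation of 0.6, none of the last two being given in the article; over correlations of 0.4 to 0.8 it runs from about 15% to 28%. The primary TUG comparison is unaffected.

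**What to change.** Replace the two regression sentences in section 2.11 with a specification along these lines:

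- **Dependent variable:** TUG at T1, continuous.
- **Independent variables:** group, TUG at T0, the freezing-of-gait stratum used in randomisation, a short pre-named set of baseline factors (at least Hoehn and Yahr stage and HAD depression, which measure the two examples in the hypothesis), and each factor's interaction with group. The interaction addresses effect modification.
- **MCID response, if also analysed:** the dependent variable of a logistic model.
- **Status:** secondary and exploratory, with a statement that interaction power is low at this sample size. Keeping the set short also limits the number of tests.

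Separately, reword the subtype cut-offs in section 2.6 so that ratios above 1.15 and below 0.90 are assigned a class, in agreement with the classification the article cites.

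The cost is wording in the protocol and any analysis plan. The variables are already collected, and neither the sample size nor the primary analysis changes.

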## Abstract

Patients with Parkinson's disease (PD) have difficulties while performing dual-task activities, a condition present in everyday life. It is possible that strategies such as transcranial Direct Current Stimulation (tDCS) can be associated with motor training enriched with dual-task training to improve the performance of two concurrent tasks. Currently, it is unclear whether specific tasks and clinical conditions of PD patients have different results after the intervention. Therefore, the proposed randomized controlled trial will examine task-dependency in enhancing the effects of tDCS-linked rehabilitation training on PD and the relationships between baseline outcomes in responders and non-responders to therapy. Fifty-six patients with Parkinson's disease will be recruited to participate in this controlled, double-blind randomized multicentric clinical trial. Patients in modified Hoehn & Yahr stage 1.5–3, age between 40 and 70 years will be included. Subjects will be randomly assigned to an experimental group (EG) and a control group (CG). The EG will perform treadmill gait training associated with dual task exercises+tDCS, while the CG will only engage in treadmill gait training+tDCS. Blinded testers will assess patients before and after 12 intervention sessions and after a 4-week follow-up period. All patients will undergo a screening and an initial visit before being assessed for primary and secondary outcomes. The primary outcome measure is functional mobility measured by Timed Up and Go Test. Secondary outcomes include cognitive function, participation, motor function and body function and structure. This study will evaluate the effectiveness of an intervention protocol with tDCS, dual-task training and gait training in patients with PD. The study will also highlight the clinical factors and variability between individuals that could interfere in the training of a specific task and influence the therapeutic effect.

**Clinical Trial registration**: www.ClinicalTrials.gov, identifier NCT04581590.

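### Section 2.11 appears to carry response into the predictor analysis as an MCID class; if so, under stated assumptions, roughly a third to a half of the information is lost, and the continuous Timed Up and Go should be modelled instead

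*Protocol article*

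**What the plan says.** Section 2.11 (Data Analyses) contains two sentences on predictors. The first names the tool: "Linear regression will be used to identify response predictors". The second lists what enters it: "The independent variables will be group and clinical response, that is, the minimal clinically important difference (MCID"). No dependent variable is named. Significance is set by "a 5% alpha (*P* < 0.05) will be established".

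The aim behind this analysis is worded in two classes. The Introduction says: "The relationships between baseline outcomes in responders and non-responders to therapy will also be examined". The Abstract likewise announces a study of "the relationships between baseline outcomes in responders and non-responders to therapy". The Introduction adds the hypothesis that disease severity and depression symptoms may affect how well treatment works. The section on limitations and advantages claims that "the study design enables secondary between-group analyses regarding baseline variables and predictors of treatment response", while conceding that the sample may be limited.

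Section 2.7 and Table 1 make the Timed Up and Go the primary outcome, collected at all three visits.

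**The concern.** An MCID is a threshold. Applied to individual patients, it normally yields reached or not reached, which matches the two-class wording of the aim. A patient just short of the threshold is then treated as the opposite of one just past it, and as the same as one who got worse. The gradation in the measurement is discarded before the association with baseline factors is examined.

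The class also fits the named tool badly. If it is the quantity to be predicted, it is a 0/1 variable in a model meant for a continuous one. If it stays among the independent variables, as the sentence literally has it, the quantity to be explained is on the wrong side of the equation and nothing is named to take its place.

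At stake is the second aim. Section 2.10 sizes the trial on the expected change in functional mobility and not on predictors, so this aim has no planned power of its own to spare.

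**Working it through.** **Inputs from the article.** N = 46 as the minimum and 56 recruited, 28 per arm (section 2.10); alpha 5% (section 2.11), taken as two-sided because the side is not stated.

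**Inputs assumed.** MCID applied to the Timed Up and Go; roughly normal change score; responder share p between 20% and 50%; one baseline predictor with correlation 0.4 with response.

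**1. The plan's own figure.** Section 2.10 says "a calculation considering *p* < 0.05 and 90% power as significant suggests that at least 46 patients would be necessary", then "we will aim to recruit 56 patients, totaling 28 participants per group". No mean difference, SD or standardised effect is printed, so 46 can only be solved backwards. With 23 per arm, d = (1.960 + 1.282) × √(2/23) = 0.96 (0.98 with the t distribution). The margin from 46 to 56 is 1 − 46/56 = 17.9%. None of this bears on predictors, and the percentage losses below do not depend on N.

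**2. Information kept after the cut.** For a normal variable split so that a share p are responders, the efficiency relative to the continuous variable is φ(z_p)² / [p(1 − p)], where φ is the standard normal density at the cut.

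| Responders | Kept | Lost | 46 patients count as | 56 patients count as |
|---|---|---|---|---|
| 50% | 0.637 | 36.3% | 29.3 | 35.7 |
| 40% | 0.622 | 37.8% | 28.6 | 34.8 |
| 30% | 0.576 | 42.4% | 26.5 | 32.2 |
| 20% | 0.490 | 51.0% | 22.5 | 27.4 |

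The last two columns are N × share kept, for example 46 × 0.637 = 29.3. Outside the assumed range the loss grows: 57.4% at 15% responders and 65.8% at 10%.

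**3. Power for one predictor.** Simulation with 20,000 replicates: a normal predictor against a normal response, tested first with the response continuous and then with it cut.

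| N | Correlation | Continuous | Cut, 50% responders | Cut, 20% responders |
|---|---|---|---|---|
| 46 | 0.4 | about 80% | 60% | 48% |
| 56 | 0.4 | 87% to 88% | 69% | 56% |
| 46 | 0.3 | 53% to 54% | 36% | 29% |
| 56 | 0.3 | 62% | 44% | 34% |

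**4. Sensitivity to shape.** The loss can also be written as 1 − cov(indicator, Y)² / [Var(Y) p(1 − p)]. At 50% responders this gives 25% for a uniform response, 46% for a t distribution with 5 degrees of freedom and 50% for a Laplace response. At 20% responders it gives 52%, 55% and 54%.

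**5. Side of the equation.** For a weak association between two variables, the loss is about the same whichever of them has been cut and whichever side it stands on. Moving response to the left-hand side would therefore not remove it.

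**The case against.** The strongest objection is that the cut is not on the page. Section 2.11 does not use the words yes/no or binary, and gives no MCID value, instrument or time point. The only model it names is linear regression, which usually has a continuous dependent variable. The regression outcome might therefore be continuous, with the responder split used only to compare baseline features. The coding may also be settled in a full protocol or analysis plan that is not shown. This stands to the extent that the cut must be called an inference. It remains the natural reading, because response is equated with a threshold, the aim is phrased in two classes, and no sentence describes a predictor analysis of continuous change. The missing MCID value is not itself faulted, since an article may leave it to the full document.

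Second, tying the MCID to the Timed Up and Go is an assumption. The Discussion speaks of predicting both motor and cognitive response. That stands, and the same argument would apply to another continuous instrument.

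Third, the share reaching an MCID answers a clinical question that a mean does not, and the article calls the study exploratory. This is fair and is a reason to keep the percentages as description. It is not a reason to base the search for predictors on them.

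A reader might go further and infer that the trial loses 36% to 51% of its information as a fixed property. The article does not support that: it gives neither a responder share nor a distribution. Nor is the primary comparison affected, because section 2.11 analyses that outcome as continuous by repeated-measures ANOVA and has ANCOVA adjust for T0.

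**Conclusion.** The point holds in conditional form. Read together, section 2.11, the Abstract and the Introduction indicate that response enters the predictor analysis as an MCID class. If it does, and if the change score is roughly normal with 20% to 50% responders, about 51% to 36% of the information is discarded. For a single predictor correlated 0.4 with response, power drops from about 80% to between 48% and 60% with 46 patients, and from about 87% to between 56% and 69% with 56.

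The responder share, the normal shape, the correlation, the single-predictor setting and the link to the Timed Up and Go are all assumptions. The loss was 25% or more in every case examined, which matters at this sample size. It concerns the second aim only. The change should be made, with medium confidence, because the cut is inferred.

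**What to change.** Rewrite the two predictor sentences in section 2.11 along these lines:

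- **Dependent variable:** the continuous post-intervention Timed Up and Go, with its T0 value as covariate. If the MCID was meant for a different instrument, use that instrument's continuous score in the same way.
- **Independent variables:** group and the baseline factors that the Introduction hypothesises, for example disease severity and depression symptoms.
- **Interactions:** add group-by-factor terms where the question is who benefits from the added dual-task training. Without them, the regression identifies who does better in general and not for whom the added component works.
- **MCID:** report the share of patients reaching it in each arm as a descriptive supplement.

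This also resolves the placement of response among the independent variables. The cost is a few sentences and no new data, since the Timed Up and Go is already measured at every visit. The small downside is that responder percentages no longer drive the search for predictors.
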